## Study Completion and Withdrawal/Dropout

1. **Subject’s Completion and Termination of Study Participation**

A subject is considered to have completed the study upon completing the follow-up visit procedures at the 24-week point after their first visit (baseline). The study is deemed complete when the last subject finishes their study participation.

1. **Subject’s Withdrawal/Dropout of Study Participation**

Subjects can discontinue their participation in the study at any time at their discretion. The investigator or sponsor can also withdraw/drop a subject’s participation at any time for safety, behavioral, or administrative reasons. The following are conditions under which a subject might be withdrawn/dropped from the study, and the investigator shall enter the collected study data into the eCRF up to the point of withdrawal/dropout:

1. A subject not meeting the inclusion/exclusion criteria was discovered during the clinical study
2. Withdrawal by subject (or his/her legal representative)
3. Non-Compliance with Investigational Product

: Subjects do not agree to or follow the investigator’s instructions related to the investigational software.

1. Lost to follow-up

: Subjects cannot be contacted for follow-up.

1. Physician Decision

If a subject is withdrawn/drops out, the investigator must notify the sponsor and make every effort to complete the end-of-study evaluation. The reasons for withdrawal/dropout must be documented in the source document and the eCRF.

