**Schedule for Data Collection in Clinical Study**

| **Collection  Schedule**  **Collection Items** | **Baseline** | **Follow-Up Visits  (Option, ☎)** | **Follow-Up Visits** | **Follow-Up Visits  (Option, ☎)** | **Close-Out Visit (COV)** |
| --- | --- | --- | --- | --- | --- |
|  | Visit 1 | Visit 2 | Visit 3 | Visit 4 | Visit 5 |
|  | 0 day | Week 6  (±2 Weeks) | Week 12 (±2 Weeks) | Week 18 (±2 Weeks) | Week 24 (±2 Weeks) |
| Obtain Written Consent^1)^ | ○ |  |  |  |  |
| Inclusion/Exclusion Criteria Confirmation | ○ |  |  |  |  |
| Assignment of Randomization Number | ○ |  |  |  |  |
| Installation of Well Check and Link to Institution | ○ |  |  |  |  |
| Demographic Information^2)^ | ○ |  |  |  |  |
| Information on Type 2 Diabetes^3)^ | ○ |  |  |  |  |
| Medical History Survey^4)^ | ○ |  |  |  |  |
| Alcohol/Smoking/Lifestyle Habits^5)^ | ○ | (○) | ○ | (○) | ○ |
| Physical Measurement^6^ | ○ | (○) | ○ | (○) | ○ |
| Vital Signs^7)^ | ○ | (○) | ○ | (○) | ○ |
| Body Composition Analysis (InBody) Test ^8)^ | (○) | (○) | (○) | (○) | (○) |
| Prior/Concomitant Medications^9)^ | ○ | (○) | ○ | (○) | ○ |
| Laboratory Tests^10)^ | ○ | (○) | ○ | (○) | ○ |
| Frequency of Well Check Use (Number of Login Days) |  |  |  |  | ○ |
| Well Check Usage Satisfaction Survey^11)^ |  |  |  |  | ○ |

*There are no additional visits or laboratory tests conducted specifically for this clinical study. In a routine clinical setting, it is recommended to collect data at 6-week intervals from Visit 1 (Baseline, Day 0) to 24 weeks (Visit 2: 6 weeks, Visit 3: 12 weeks, Visit 4: 18 weeks, Visit 5: 24 weeks). Visit 2 (6 weeks) and Visit 4 (18 weeks) can be optional visits and data can be collected via phone calls, based on the investigator (responsible physician )'s discretion. If a subject withdraws or drops out from the study, the data collected up to that point should be recorded in the case report form to the maximum extent possible.

1. Written consent must be obtained before performing any clinical study procedures. The date of written consent and Visit 1 (Baseline, Day 0) may differ, but consent must be obtained before participation in the clinical study.
2. Collect demographic information [initials, gender, age (month and year of birth), pregnancy and breastfeeding status].
3. Collect information on Type 2 Diabetes (date of diagnosis).
4. Collect medical history within 6 months prior to Visit 1 (Baseline, Day 0).

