# Clinical Study Method

## Overall Study Design

This clinical study is designed as a primary care-based, prospective, multicenter, cluster-randomized, pragmatic clinical trial to confirm the improvement effects on blood glucose, blood pressure, and weight over 24 weeks in patients with Type 2 Diabetes when using ‘Well Check’ with or without investigator-linked management in real-world primary care settings.

Eligible subjects include patients currently being treated with Envlo Tab. or Envlomet SR Tab. for Type 2 Diabetes or those deemed eligible for such treatment by the investigator (responsible physician). Subjects must also be able to use the digital healthcare smartphone application without difficulty.

Due to the practical constraints of primary care settings, where it is challenging to manage test group and control groups separately within the same institution, cluster randomization will be used. Institutions will be randomized as either the test group [institutions managing subjects with the 'Well Check' app in conjunction with the investigator (responsible physician)] or the control group (institutions where subjects use the 'Well Check' app for self-management). The study will be conducted following this setup.

[figure not shown]

Study Subjects

Use of 'Well Check'
for Simple Self-Management

(Control Group Institutions)

Investigator
(Responsible Physician)

Use of 'Well Check'
for Integrated Management
(Study Group Institutions)

Cluster Randomization

Participating Institutions

(Primary Care Institutions)

Figure 1. Clinical Study Design

Data collection for this clinical study will be based on medical records documented during routine clinical visits. Collected data will include demographic information, physical measurements, vital signs, and laboratory test results. There are no mandatory visits, tests, or treatments specified by this study.

However, prospective data collection through follow-up visits will be conducted up to 24 weeks from the baseline registration date.

The planned time points for prospective data collection are baseline (0 days), visit 2 (6 weeks), visit 3 (12 weeks), visit 4 (18 weeks), and visit 5 (24 weeks). Visits 2 and 4 can be optionally collected based on the investigator (responsible physician)'s judgment and allow for telephone follow-ups.

[figure not shown]

Visit 1

(0 days)

Visit 2

(6±2 weeks)

Visit 3

(12±2 weeks)

Visit 4

(18±2 weeks)

Visit 5

(24±2 weeks)

Baseline

Follow-Up Visits

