## Study Procedure and Schedule

### Visit Schedule

There are no mandatory visits, tests, or treatments specified by this study. Data will be prospectively collected using medical records, investigator assessments, and laboratory test results from routine clinical visits. Each investigator will collect predefined information from subjects at baseline and during the follow-up period.

1. **Visit 1 (Baseline, Day 0)**

At the first visit (baseline), the following information will be collected:

- Obtain subject consent and assign subject enrollment number
- Inclusion/Exclusion Criteria Confirmation
- Installation and Hospital Integration of the Digital Healthcare Smartphone Application ‘Well Check’
- Demographic information [initials, gender, age (month and year of birth), pregnancy and breastfeeding status].
- Information on Type 2 Diabetes (Diagnosis date)
- Medical history (Past medical history within 6 months prior to enrollment (excluding the target disease) and current medical history)
- Alcohol/Smoking/Lifestyle information
- Physical measurements (height, weight, BMI)
- Vital signs (systolic/diastolic blood pressure, pulse rate)
- Body composition analysis (include skeletal muscle mass, body fat mass, body fat percentage, muscle mass, waist/hip circumference, body water, intracellular water, extracellular water, extracellular water ratio, abdominal fat percentage, etc.)
- Prior medications (diabetes treatments within 4 weeks prior to enrollment) and concomitant medications (all medications, including diabetes treatments, taken at the time of enrollment).
- Laboratory tests (HbA1c, FPG, Total Cholesterol, LDL-C, HDL-C, Triglyceride, ALT, AST, Creatinine, e GFR, UACR, UGCR, etc.)

1. **Follow-Up Visits**

Follow-up visits will be conducted at 6-week intervals from the first visit (baseline) as Visit 2 (6 weeks ±2 weeks), Visit 3 (12 weeks ±2 weeks), Visit 4 (18 weeks ±2 weeks), and Visit 5 (24 weeks ±2 weeks). Visits 2 and 4 may be optional and data collection can be conducted via phone calls, based on the investigator (responsible physician)’s discretion. During follow-up visits, the following information will be collected:

- Alcohol/Smoking/Lifestyle information
- Physical measurements (weight, BMI)
- Vital signs (systolic/diastolic blood pressure, pulse rate)

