**[Control Group]**

For the control group, the basic usage of the 'Well Check' smartphone application is recommended as follows. Subjects are encouraged to use the 'Well Check' app in a self-recording format. The investigator will not monitor or utilize the subject's use of 'Well Check' during the study period.

1. Visit 1 (Baseline, Day 0) to Visit 5 (Close-out Visit, 24 weeks)

- No specific guidance or settings for the 'Well Check' application are provided; subjects use it freely for self-recording
- Investigator (Responsible Physician): No separate management or consultation via 'Well Check Doctor Web'; routine medical care is provided
- Automatic dispatch of subject educational materials (twice weekly)

1. **Demographic Information**

At Visit 1 (Baseline, Day 0), the following information is collected to verify the subject's basic information. Pregnancy status is collected through interview or existing pregnancy test results, if available.

- Initials
- Gender
- Month and year of birth, age
- Pregnancy and breastfeeding status

1. **Information on Type 2 Diabetes**

Collect the diagnosis date of type 2 Diabetes at Visit 1 (Baseline, Day 0).

1. **Medical History Review**

For medical history, any clinically significant medical conditions or abnormalities observed before Visit 1 (Baseline, Day 0), excluding the target disease, will be defined. The diagnosis name and date of each condition will be collected for medical history within 6 months prior to Visit 1 (Baseline, Day 0) and ongoing conditions.

1. **Alcohol/Smoking/Lifestyle Information**

At Visit 1 (Baseline, Day 0), the following information is collected to verify the subject's basic information, and any changes will be additionally collected at each subsequent visit. Verify through routine medical visits, medical records, and for the test group, data collected within the 'Well Check' application can be utilized.

1. Drinking history
   - Current Drinker*: ≥ 12 glasses (units) in a lifetime and drinking at least once in the last 12 months
   - Former Drinker: Has consumed at least 12 units of alcohol in their lifetime but has not drunk in the past 12 months
   - Non-Drinker: < 12 glasses (units) in a lifetime

^*^ For current drinkers, the weekly drinking frequency and amount per occasion will be confirmed.

1. Smoking history
   - Current Smoker: Has smoked ≥ 5 packs (100 cigarettes) in a lifetime and smoked within the past 30 days

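### Section 3.5 limits data entry to the time before withdrawal on every ground, so routine week-24 HbA1c values may be left out, possibly more often in the test arm

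*Protocol*

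**What the plan says.** Section 3.5 (Study Completion and Withdrawal/Dropout) lists five grounds: ineligibility discovered later, the subject's own withdrawal, non-compliance, loss to follow-up and physician decision. It also lets the investigator or sponsor withdraw a patient for safety, behavioural or administrative reasons. One data rule introduces the whole list: "the investigator shall enter the collected study data into the eCRF up to the point of withdrawal/dropout". The note under the Schedule for Data Collection repeats it without distinguishing reasons: "the data collected up to that point should be recorded in the case report form to the maximum extent possible".

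Section 3.5 then adds that, for a withdrawn patient, the investigator must "make every effort to complete the end-of-study evaluation". It does not say whether this means at the time of leaving or at week 24.

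On the source of data, section 4.1 states: "Data collection for this clinical study will be based on medical records documented during routine clinical visits". Section 4.3 agrees: "Data will be prospectively collected using medical records, investigator assessments, and laboratory test results from routine clinical visits". Section 8.8 says that care runs independently of the study and continues during and after it. Section 4.1 also states: "There are no mandatory visits, tests, or treatments specified by this study".

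Section 3.5 describes non-compliance as follows: "Subjects do not agree to or follow the investigator’s instructions related to the investigational software". In section 4.4 the test group has a recommended programme of daily glucose entries, weekly blood pressure and weight entries, education and physician messages. For controls the section says: "No specific guidance or settings for the 'Well Check' application are provided; subjects use it freely for self-recording".

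**The concern.** The protocol nowhere separates a patient who stops using the app, or stops study procedures, from one who withdraws consent to the use of data. Only the second clearly requires data entry to end. In a trial that reads its primary outcome from the clinic's own records, a patient who has left the intervention can often be followed at almost no cost. A site that follows section 3.5 to the letter would not do so.

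At stake is bias in the primary comparison, the change in HbA1c at 24 weeks. One of the grounds depends on behaviour after randomization and on instructions that only the test arm receives. If poorly engaged test patients are withdrawn on that ground and their later values are not entered, the test patients who remain are a selected group with no matching selection among controls. An analysis plan cannot recover values that sites did not enter.

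**Working it through.** **1. The plan's sample size (section 3.2).** Inputs: difference 0.4, SD 1.1, ICC 0.02, 20 patients per clinic, 20% dropout; 24 clinics (synopsis); two-sided 5% level (section 7.2). The readable text gives no power.

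- A two-sample t-test gives exactly 274 in total at power 0.85, so 0.85 is taken as the implied power.
- Design effect: 1 + (20 − 1) × 0.02 = 1.38; 274 × 1.38 = 378.
- Dropout: 378 / 0.80 = 472.5, or 473. The planned 480 equals 24 × 20.

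The plan's figures reproduce.

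**2. Power.** Effective size is the number analysed divided by 1.38 (normal approximation). How many of the lost 20% have a usable record is not in the documents, so the range is shown.

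| Lost values recovered | Analysed | Effective size | Power |
|---|---|---|---|
| none | 480 × 0.80 = 384 | 278 | 0.858 |
| half | 432 | 313 | 0.896 |
| all | 480 | 348 | 0.924 |

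Even with nothing recovered, power stays at the implied 0.85.

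**3. Which grounds matter.**

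- *Found ineligible:* outside the efficacy set (section 7.2) in any case.
- *Withdrawal by the subject:* may include consent to data use, in which case stopping can be required.
- *Lost to follow-up:* there may be no later record.
- *Non-compliance, physician decision, sponsor or administrative withdrawal:* the patient may remain in care, and a routine HbA1c may be on file.

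The recoverable loss lies mainly in the last group.

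**4. Size of the possible bias.** Let f be the excess share lost in the test arm, and g the amount by which lost patients' week-24 HbA1c is worse than that of retained patients. The full test-arm mean equals the retained mean plus f × g, so a complete-case comparison overstates the benefit by f × g. The same formula holds when both arms lose patients with the same gap g and f is the difference in loss. Both f and g are assumptions.

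| f | g = 0.2 | g = 0.4 | g = 0.8 |
|---|---|---|---|
| 5% | 0.01 | 0.02 | 0.04 |
| 10% | 0.02 | 0.04 | 0.08 |
| 20% | 0.04 | 0.08 | 0.16 |

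Against the planned 0.4, this runs from 0.01 / 0.4 = 2.5% to 0.16 / 0.4 = 40%. With 480 / 2 = 240 patients per arm, f = 5% is 12 test patients and f = 20% is 48.

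**5. The two sentences of section 3.5 side by side.** If the end-of-study evaluation means Visit 5, it asks for data after the point at which the entry rule stops. If it means an evaluation on leaving, the two sentences agree, but the value may fall well before week 22. The text does not settle which is meant.

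**The case against.** The strongest reply is that neither sentence forbids later entry. Both can be read as a duty to save what has been collected. The end-of-study evaluation may already mean Visit 5: section 4.3 ties the end of study to the satisfaction survey, and section 4.4 places that survey at Visit 5, week 24. On this reading the protocol already asks sites to try for the week-24 value. That is a fair reading, and it makes the point one of reconciliation. It does not remove the problem, because a site can equally follow the cut-off.

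A reader might infer that the missing values will exist. The documents do not show this: no test is mandatory, laboratory results are collected only if done in routine care, and nothing says that withdrawn patients stay at the same clinic. The supportable claim is that some values may exist.

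A reader might also infer that an HbA1c taken on leaving, say at week 8, would stand as the week-24 result, because the efficacy set accepts any post-baseline HbA1c. That definition decides who is analysed and does not assign a value to week 24. Visit 5 is 24±2 weeks, and no text maps an early value to it.

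On size, the upper corner is demanding. A 20-point excess around 20% average loss means about 30% against 10%, and nothing in the protocol suggests that. The formula is also for a complete-case analysis, whereas section 7.2 plans multiple imputation when missing data are substantial or uneven, plus sensitivity analyses. This stands. The table gives a range for one scenario and is not the error of the planned analysis, so no false-positive rate should be read from it. Standard imputation works from observed data, however, and does not correct loss that depends on the unseen HbA1c.

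**Conclusion.** The point holds in a limited form. Section 3.5 and the schedule note set one cut-off for every ground, and section 3.5 also contains an undated instruction that may point the other way. As written, the rule can leave out routine week-24 HbA1c values, mainly for patients withdrawn for non-compliance, by physician decision or for administrative reasons. The non-compliance ground can arise mainly in the test arm, so the loss can be uneven.

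The size is 0.01 to 0.16 HbA1c points in a complete-case comparison, against a planned 0.4. It rests on an assumed excess loss of 5 to 20 percentage points and an assumed gap of 0.2 to 0.8. The direction, in favour of the intervention, rests on non-compliant patients having worse HbA1c than those who stay. Imputation may make the bias smaller. Power is not affected, because the 20% loss is already in the sample size. The wording is worth changing because the remedy is cheap and an observed value is better than an imputed one.

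**What to change.** In section 3.5 and the schedule note:

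- Separate stopping app use or study procedures, on any ground, from withdrawing consent to data use.
- In the first case, keep entering any HbA1c available in the clinic's routine record through Visit 5 (24±2 weeks). Stop entry only when consent to data use is withdrawn.
- State that the end-of-study evaluation means the Visit 5 window. Record any earlier evaluation with its actual date, so that it is not taken as the week-24 value.

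The cost is protocol and consent wording, a way to label an early evaluation in the eCRF, and some chart look-up for patients who stopped. No visit or test is added. The consent form is not among the documents reviewed, so its present wording on data after withdrawal should be checked first.

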### Efficacy Analysis Set

Subjects who meet the inclusion/exclusion criteria, have been enrolled in this study, received the investigational product at least once, and have had their HbA1c level collected post-baseline will be included in the efficacy analysis set.

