### Safety Analysis Set

Subjects who meet the inclusion/exclusion criteria, have been enrolled in this study, received the investigational product at least once according to the approved indications, and have undergone safety evaluations will be included in the safety analysis set.

1. **Methods of Analysis**
2. **General Principles**

Continuous variables will be presented as descriptive statistics (number of subjects, mean, standard deviation, median, minimum, maximum), and categorical variables will be presented as frequencies and percentages. Unless otherwise specified, all tests will be two-sided with a significance level of 5%. All p-values will be reported to a maximum of three decimal places. If not exactly divisible, values will be rounded to two decimal places, rounding up at the third decimal place.

If missing data is minimal and evenly distributed, a complete-case analysis will be considered; multiple imputation methods will be employed if missing data is substantial or disproportionately distributed between groups. Sensitivity analyses will also be performed to ensure the robustness and validity of conclusions under various missing-data scenarios.

1. **Demographic and Baseline Characteristics**

For the demographic data (age, gender, etc.) and baseline characteristics of the study subjects, continuous variables will be presented as mean, standard deviation, median, minimum, and maximum values, while categorical variables will be presented as frequency and percentage.

To assess baseline comparability between intervention and control groups, standardized mean differences (SMDs) will be calculated for key baseline characteristics, including age, sex, HbA1c, BMI, and diabetes duration. Variables exhibiting significant imbalance between groups (SMD > 0.1) will be included as covariates in subsequent analyses.

1. **Efficacy Endpoints**

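### Withdrawal for software non-compliance, likelier to be met in the test arm, combined with an efficacy set that requires a post-baseline HbA1c, exposes the primary comparison to selection after randomisation

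*Protocol*

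**What the plan says.** **Withdrawal (Protocol 3.5).** "The investigator or sponsor can also withdraw/drop a subject’s participation at any time for safety, behavioral, or administrative reasons". The listed conditions, introduced permissively, include "Non-Compliance with Investigational Product", explained as: "Subjects do not agree to or follow the investigator’s instructions related to the investigational software". On withdrawal, "the investigator shall enter the collected study data into the eCRF up to the point of withdrawal/dropout", and the investigator must also "make every effort to complete the end-of-study evaluation".

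**What each arm is asked to do (Protocol 4.4).** All subjects install the app, register and link it to the clinic. Test subjects are then recommended to record glucose every day, blood pressure and weight every week, and medication as taken, and to complete education twice a week. Their physicians review the records and message those who do not measure. For control subjects the entry begins "No specific guidance or settings for the" app; they self-record as they like, and the physician does not monitor or use their app data.

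**Analysis set (Protocol 7.2, Efficacy Analysis Set).** Enrolled subjects who meet the eligibility criteria, "received the investigational product at least once, and have had their HbA1c level collected post-baseline will be included in the efficacy analysis set". No other efficacy set is defined.

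**Missing data (Protocol 7.2, General Principles).** "If missing data is minimal and evenly distributed, a complete-case analysis will be considered". Multiple imputation applies if missingness is substantial or uneven between groups, and sensitivity analyses under several missing-data scenarios are promised.

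**Availability of HbA1c (Protocol 4.1 and 4.3).** No visit or test is mandatory. Visits 2 and 4 are optional and may be done by telephone.

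**The concern.** The trial is described as pragmatic and compares clinics allocated to linked management with clinics allocated to self-management. Patients who lose interest in the app are part of that effect. A withdrawal ground tied to app behaviour, in a design where only one arm has continuing app instructions and someone watching, can remove such patients more readily from that arm. The efficacy set then makes some of these removals permanent, because a patient with no HbA1c after baseline is outside the set altogether.

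What is at stake is the primary endpoint. The comparison would no longer be between patients as their clinics were allocated, but between those who remained observable in each arm, and what makes a patient observable differs by arm. Outcomes not collected after withdrawal may not be recoverable later.

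**Working it through.** **1. Tracing a patient through the rules.**

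| Step | Test arm | Control arm |
|---|---|---|
| Install, register, link | Yes | Yes |
| Continuing app tasks | Daily, weekly and twice-weekly | None specified |
| Physician sees app use | Yes, and prompts non-users | No |
| Non-compliance ground can be met | At set-up and throughout | Mainly at set-up |
| Dropped after an interim HbA1c | In the set; week 24 can be imputed | Same |
| Dropped before any later HbA1c | Outside the set | Same |

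The asymmetry lies in how likely the ground is to be met and detected. The first non-optional visit after baseline is Visit 3 at 12 ± 2 weeks, so a patient who disengages before roughly weeks 10 to 14 may have no post-baseline HbA1c.

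**2. The plan's own figures (section 3.2).** Inputs: difference 0.4, SD 1.1, two-sided 5%, ICC 0.02, cluster size 20, dropout 20%. The text states no power. A two-sample t-test needs 240, 274 and 320 patients at 80%, 85% and 90% power, so the stated 274 corresponds to 85%. Design effect: 1 + (20 − 1) × 0.02 = 1.38. Then 274 × 1.38 = 378.1, and 378 / 0.8 = 472.5, rounded up to 473, against a target of about 480 (24 sites × 20). The arithmetic is not at fault. The 20% dropout is not split by arm or reason.

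**3. Size of a possible bias (illustration).** Let q be the share of test patients wholly lost from the analysis, and g the amount by which their HbA1c change is worse than that of retained test patients. Neither is in the documents. The full-arm mean change is (1 − q)r + q(r + g) = r + qg, where r is the retained mean, so analysing only retained patients shifts the difference by **q × g** toward the test arm.

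Precision: 378 / 1.38 = 273.9 effective patients, about 137 per arm. With no losses, SE = 1.1 × √(2/137) = 0.133. With losses, the test-arm number is multiplied by (1 − q). Normal approximation, true effect zero, nominal 2.5% chance of a false result favouring the test arm:

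| q | g | Bias (points) | Share of 0.4 | False result favouring test |
|---|---|---|---|---|
| 5% | 0.4 | 0.02 | 5% | 3.5% |
| 10% | 0.4 | 0.04 | 10% | 4.8% |
| 20% | 0.4 | 0.08 | 20% | 8.2% |
| 5% | 0.8 | 0.04 | 10% | 4.8% |
| 10% | 0.8 | 0.08 | 20% | 8.5% |
| 20% | 0.8 | 0.16 | 40% | 20.5% |

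With g = 0 there is no bias. With g = −0.4 it reverses, from −0.02 to −0.08 over the same q.

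**4. Loss in both arms.** With losses in each arm the net shift is q_T × g_T − q_C × g_C. If 5% are lost from test and 10% from control, both with g = 0.4, it is 0.02 − 0.04 = −0.02, against the test arm. The sign depends on which arm loses more, and on how those patients fare.

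**The case against.** A reader might infer that the rule can remove patients from one arm only, that the bias certainly favours the test arm, and that the planned imputation is no help. The documents do not support any of these in full.

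- **One arm only.** Both arms must install and link the app, and refusal to agree to instructions is possible in either. Withdrawal is permissive. Test-arm use is recommended, and for insufficient recording section 4.4 mentions encouragement by message, not withdrawal. The difference is one of likelihood, though a large one.
- **Direction.** Having an HbA1c also depends on how closely the clinic follows the patient. Closer follow-up in test clinics could yield more HbA1c values there and lose disengaged controls instead. The protocol gives no data on how non-users fare, and the endpoint is change, so poorer control at baseline does not settle the sign.
- **Safeguards.** Complete-case analysis is conditional; a loss of 10-20% from one arm, if counted as missing, would call for multiple imputation. The set asks for any post-baseline HbA1c, not one at week 24, so a patient dropped after an interim value can be imputed. Section 3.5 also requires an effort to complete the final evaluation.
- **Size.** The table treats every removed patient as wholly lost and not imputed. Its upper end gives the whole 20% dropout allowance to this one ground, with an outcome gap twice the planned effect.

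These points limit the claim but do not remove it. The effort clause guarantees no HbA1c. The protocol does not extend imputation beyond the efficacy set, so a patient with no post-baseline value is neither imputed nor, on a plain reading, counted as missing. The sensitivity analyses are not tied to any wider set. Nor is this a detail awaiting an analysis plan, since the protocol fixes the set itself.

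**Conclusion.** The concern holds as a structural weakness. A withdrawal ground far more likely to be met and detected in the test arm is joined to a sole efficacy set that depends on an event after randomisation, so the comparison by allocated clinic is not protected against selection.

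The direction is uncertain. Bias favours the test arm if disengaged test patients do worse and are lost more often than their control counterparts; it can go the other way if closer follow-up preserves more HbA1c values in the test arm. The range of 0.02-0.16 points (5-40% of the planned difference) is an upper illustration resting on an assumed 5-20% loss confined to the test arm, an assumed gap of 0.4-0.8 points, and no recovery by imputation. It is not an estimate for this trial. Severity: should be fixed, with moderate confidence.

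**What to change.** **Section 3.5.** State that non-compliance with the software affects app use only, and that routine-care HbA1c continues to be collected to week 24 unless the patient withdraws consent. The arm-asymmetry argument gives no reason to delete later-found ineligibility as a withdrawal ground, so that is not proposed.

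**Section 7.2.** Define the primary efficacy set as all enrolled patients, analysed in their clinic's allocated arm. Handle missing week-24 HbA1c with a likelihood-based mixed model or multilevel multiple imputation, using baseline and any interim HbA1c. If the mixed model is chosen, baseline should be among the modelled responses; a model of change with baseline only as a covariate would again drop patients who have no later value. Keep the present set and the complete-case analysis as supportive, and report by arm the numbers enrolled, withdrawn by reason, and with an HbA1c at week 24.

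**Cost.** A protocol amendment with IRB approval and some analysis work. The HbA1c values come from routine care, so no visits or tests are added; values never measured in routine care will still be missing and must rest on the imputation model. The estimated effect may be smaller than under the present set.
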